#### Observation schedule and procedure

Informed by data from the feasibility study, observations will be conducted over 2 days, four times a day (weekdays only) at each time point, resulting in a total of eight observation periods for each site at each time point. Observations will be conducted at four set observation periods per day: morning (10-11 am), lunchtime (12-1 pm), afternoon (3-4 pm), and evening (5-6 pm). These times were found to capture the biggest variation in older adults’ activity across the day (Fig. 1), whilst also providing sufficient time for breaks and possible travel to other sites in between observation periods.

Observations for each intervention site and the two corresponding comparison sites will be spread over 2 weeks. This will provide a more robust assessment of activity over a longer period rather than observing activity during a single week. Observations will be counterbalanced to control for week, day of week and time of day. The observation schedule used for baseline data collection is displayed in Fig. 3; this schedule will be replicated at all follow-ups. Any missed observations (e.g. due to illness) will be rescheduled for the same day of the next available week.

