#### Main analysis

The analysis will estimate the effect of the intervention on the number of older adults using the site at each of the two time points, and the types of behaviours they engage in per observation period, compared to the two corresponding comparison sites. The analysis will control for known confounders including weather, day and time. The primary analysis will analyse data for older adults and a secondary analysis will analyse data for all adults using the same methods.

The primary outcome will be a count per observation period of Take Notice behaviour at 12 months. Take Notice behaviour is the primary outcome because the interventions are expected to improve the aesthetic quality of green space by providing visual information of value to users, thus causing more overt appreciation in the intervention sites. The secondary outcome will be the overall count of older adults per observation period. Additional exploratory analyses will assess a count per observation period separately for each physical activity level (Sedentary, Walking, Vigorous) and Connect behaviour.

For each outcome we will follow three steps. Firstly, using a dataset that only includes the baseline data, and is blinded to group allocation, we will build a regression model to examine the relationship between the baseline count outcome and the covariates (weather, day, time). The overall count of older adults per observation period will be used as an additional covariate when analysing each of the behaviours (i.e. Sedentary, Walking, Vigorous, Take Notice, Connect). We will consider this count outcome as either a poisson distribution, a zero-inflated poisson or a normal distribution. We will consider all these approaches, and we will choose the most suitable approach by seeing which model has the best fit, assessed using Akaike’s information criterion (AIC) and measures of over-dispersion. Secondly, once we have developed a suitable model with the baseline data, we will combine the pre- and post-intervention data together and apply the model from step one. Thirdly, we will add into the model Group (intervention or comparison) and Period (pre or post). The treatment effect will be the coefficient for the interaction of Group and Period. This is a form of Difference in Differences analysis [48, 49], adapted because we do not have a before and after measure at the level of the hour.

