A power calculation showed that if we match four intervention sites and eight comparison sites (12 in total) and have eight observation periods per cluster, we will have 99% power (*p* = .05, two-tailed test) to detect a difference between 0.5 (SD = .77) counts per observation period of Take Notice behaviour in older adults in the control group and 1.6 (SD = 1.72) in the intervention group. This assumes the ICC is 0.02, *p* = .05, two-tailed test: this low ICC value has been used in previous studies that have evaluated homogeneous parks ([name], personal communication). This also assumes that the ‘comparison’ group and ‘intervention’ groups from the feasibility study accurately represent the comparison and intervention sites in the main study at follow-up. However, due to the lack of data from previous studies on changes in older adult’s Take Notice behaviours in urban street greening interventions, data from the feasibility data was the most suitable available data to inform the power calculation.

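### For very sparse outcomes (below about 0.13 events per hour), AIC does not fairly compare the normal model with the count models, and the plan does not say how over-dispersion would settle the choice

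*Protocol article*

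**What the plan says.** The Main analysis section of the protocol article sets out a model-building procedure that applies throughout: "For each outcome we will follow three steps". The outcomes are Take Notice (primary), the overall count of older adults (secondary), and exploratory counts taken "separately for each physical activity level (Sedentary, Walking, Vigorous) and Connect behaviour".

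The first step works "using a dataset that only includes the baseline data, and is blinded to group allocation". Three candidates are named: "We will consider this count outcome as either a poisson distribution, a zero-inflated poisson or a normal distribution". The selection rule is that "we will choose the most suitable approach by seeing which model has the best fit", judged by Akaike's "information criterion (AIC) and measures of over-dispersion". The section gives no order or weight between these two criteria. It also does not say how a normal likelihood is made comparable with a count likelihood.

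The chosen model is then applied to the combined data, and the treatment effect is the Group by Period interaction coefficient. The only planning rates in the article are for Take Notice, in the Power calculation section: 0.5 per hour (SD .77) and 1.6 per hour (SD 1.72).

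**The concern.** A Poisson or zero-inflated Poisson log-likelihood is a sum of log probabilities, each at most zero. A normal log-likelihood is a sum of log densities, which can be positive. For counts spaced by one unit, the density is a fair stand-in for the probability of a count unless the SD is small. When nearly every hour records zero, the SD is small, and the normal model gains AIC from the change of scale and not from fit.

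The model also fixes the meaning of the reported effect. Under a normal model the interaction is a difference in counts per hour. Under a Poisson model with the usual log link (an assumption, since the article names no link) it is a log rate ratio. For a very sparse outcome, an artefact could therefore decide the effect measure. The normal model would also bring constant variance and some negative fitted counts.

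**Working it through.** **Inputs.** There are 12 sites (Study design; Power calculation), with "resulting in a total of eight observation periods for each site at each time point". The baseline sample is 12 × 8 = 96 periods. Each time point has 4 × 8 = 32 intervention periods and 8 × 8 = 64 comparison periods. No rates are given for outcomes other than Take Notice, so 0.02 to 0.2 per hour is an assumed range. The article states no figure for the selection rule, so there is none to reproduce.

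**1. Where the scales part.** The peak of a normal density is 1/(SD × √(2π)). It exceeds 1 when SD < 1/√(2π) ≈ 0.40.

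**2. Expected AIC difference for Poisson data, intercept only.** AIC(normal) − AIC(Poisson) ≈ 2n(H_N − H_P) + 2, with n = 96, H_N = ½ ln(2πe·m) and H_P = −Σ p ln p. The +2 is for the extra variance parameter. At m = 0.10 this is 192 × (0.268 − 0.334) + 2 ≈ −10.7.

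| Mean per hour | H_N | H_P | AIC difference |
|---|---|---|---|
| 0.02 | −0.537 | 0.098 | −120 |
| 0.05 | −0.079 | 0.201 | −52 |
| 0.10 | 0.268 | 0.334 | −11 |
| 0.15 | 0.470 | 0.442 | +7 |
| 0.20 | 0.614 | 0.535 | +17 |
| 0.50 | 1.072 | 0.928 | +30 |
| 1.60 | 1.654 | 1.577 | +17 |

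Negative values favour normal. The sign changes at 0.131 per hour without the penalty and 0.125 with it, which is about 12 events in 96 periods.

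**3. Simulated choice by lowest AIC.** Poisson data, 300 datasets per rate (those with no events dropped), Poisson, zero-inflated Poisson and normal as candidates. The last column replaces the normal density by the probability of the interval from y − 0.5 to y + 0.5.

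| Mean per hour | Normal chosen, density | Normal chosen, interval probability |
|---|---|---|
| 0.03 | 100% | 0% |
| 0.05 | 99.7% | 0% |
| 0.10 | 76% | 4% |
| 0.15 | 46% | 14% |
| 0.20 | 21% | 16% |
| 0.30 | 2% | 2% |
| 0.50 | 0% | 0% |
| 1.60 | 2% | 2% |

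With over-dispersed (negative binomial) data, normal is chosen in 53% at mean 0.10 (SD 0.35) and 87% at mean 0.05 (SD 0.25) on the density scale, against 1% and 0% on the interval scale. At the plan's own values, 0.5 (SD .77) and 1.6 (SD 1.72), it is 0% either way.

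A second simulation compared normal with Poisson only, with the outcome as a thinning of an assumed total of 6 per hour and with day, time, rain and total count as covariates. Normal was chosen in 100%, 99%, 78%, 38% and 19% at 0.03, 0.05, 0.10, 0.15 and 0.20, so covariates barely move the result. Site clustering was not modelled.

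**4. The over-dispersion criterion.** In the sparse Poisson simulations the Pearson dispersion averaged about 1.0 at every rate. It gives no reason to reject Poisson while AIC points to normal. The article does not say which prevails.

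**5. Coverage if normal is used.** Poisson data, cells of 32, 32, 64 and 64; the rate goes from 0.1 to 0.3 in the intervention group and stays at 0.1 elsewhere.
- True variance of the interaction: 0.1/32 + 0.3/32 + 0.1/64 + 0.1/64 = 0.015625, so SE = 0.125.
- Pooled variance: (32 × 0.1 + 32 × 0.3 + 128 × 0.1)/192 = 0.1333. Least-squares variance: 0.1333 × (2/32 + 2/64) = 0.0125, so SE = 0.112.
- Ratio 0.894, so a nominal 95% interval covers 2Φ(1.96 × 0.894) − 1 ≈ 92%.

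With no effect all four cells share one variance and the ratio is 1. Simulated coverage is then 95.2% at 0.05 and 95.3% at 0.10.

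**6. What the count model faces at these rates.** With a constant rate m, the chance that at least one cell has no events is 1 − (1 − e^(−32m))² × (1 − e^(−64m))². This is 72% at 0.03, 41% at 0.05 and 8% at 0.10. The log-scale interaction is then infinite.

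**The case against.** Four points can be made for the plan.

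- AIC is not the only criterion. A dispersion statistic near 1 would support Poisson, and an analyst might act on it. This stands in part: it means the plan does not commit to the AIC choice. But the text leaves the conflict unresolved.
- Selection uses blinded baseline data, so it cannot be steered by the treatment effect. That stands, but blinding does not cure a scale mismatch.
- Harm is limited. Type I error is preserved, and under-coverage needs a large relative effect: about 93% when 0.1 doubles and 92% when it triples. The Power calculation section itself expects small effects. This stands.
- At the rates where normal is wrongly favoured, the count model often cannot estimate the interaction. This also stands. It shapes the repair but does not make the selection rule valid.

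A reader might infer that the primary analysis will use the wrong model. The documents do not support that: at 0.5 per hour AIC favours Poisson over normal by about 30 points if the data are Poisson. A reader might also infer that Vigorous or Sedentary activity is certainly rare enough to be affected. The Outcome measure section describes small sites with few users, which makes sparsity plausible, but no rate is given.

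**Conclusion.** The point holds for very sparse outcomes only. Below roughly 0.13 events per hour the AIC part of the rule leans to the normal model because of scale. By 0.3 per hour the artefact has gone. Take Notice would be exposed only if its baseline rate were about a quarter of the planned value (0.13/0.5 ≈ 0.26) or less. No figure in the article suggests this, although 0.5 comes from a single feasibility site. The likely exposure is in exploratory outcomes of unknown rate.

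The main cost is that the effect measure, a difference in counts or a rate ratio, could be set by an artefact. The loss of coverage is moderate and appears only with a true effect. These figures assume independent periods without site clustering, and the 0.02 to 0.2 range is an assumption. The gap in the text, how AIC and over-dispersion combine, exists at any rate.

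**What to change.** Change the selection sentence in the Main analysis section in three ways.

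1. Use AIC only among the discrete count models. Alternatively, keep the normal model but compute its likelihood as the probability of the unit interval around each count, so that all AIC values share one scale.
2. State how AIC and over-dispersion combine, including which prevails when they disagree.
3. State in advance that outcomes too sparse for the Group by Period term to be estimated, at about 0.05 per hour or below, will be reported descriptively or with an exact or penalised method.

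The cost is a few lines of text, some programming for the interval likelihood if that option is taken, and no new data. At 0.3 per hour or more, the interval version made the same choices as the present rule in every scenario run. Restricting AIC to count models has one further consequence: it removes the normal option for busier outcomes too. In over-dispersed data with an assumed mean of 5 (variance = mean + 0.3 × mean²), normal was preferred to Poisson and zero-inflated Poisson in 95% of datasets on either scale, so that preference is not a scale artefact. If the normal model is wanted for such outcomes, the interval version keeps it available.

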## Methods (main study)

### Study design

This is a prospective controlled before and after natural experimental study of the effects of changes in urban green space, with four intervention and eight matched comparison sites in GM: two comparison sites per intervention site.

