### Power calculation

Given the lack of previous studies of the causal effects of urban street greening, it is difficult to estimate the plausible size of the effect that interventions will have on the outcomes. However, the interventions only target one known variable that can influence physical activity and wellbeing within the context of a broader complex ‘system’ [50]; therefore, the effects on the measured outcomes, particularly physical activity, are likely to be small.

To assess the power of the study, we conducted a power calculation of the primary outcome measure: counts per observation period (hour) of Take Notice behaviour in older adults. We used the approach suggested by Donner and Klar ([51], p.66) for calculating the sample size for a matched pair design: calculate the number of clusters required for a completely randomised cluster design, and then multiply that by one minus the correlation between the mean outcomes in the two groups. This suits our context because it allows us to account for multiple comparison groups for each intervention group. We used the means and standard deviations (SD) from the two sites in the feasibility study. We assumed that one site was the ‘comparison’ group (i.e. the intervention site at baseline) and the other site was the ‘intervention’ group (this site had two benches, more greenery and was thus more aesthetically appealing based on ratings using the NGST). For the SDs for each site, we used the 80% upper one-sided confidence limit of the SD to account for the possibility that the SD from the feasibility data may be an underestimate.

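### The primary Group-by-Period model has no site or matched-set term, so its standard error is not protected against site-level variation in a 12-site matched design

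*Protocol article*

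**What the plan says.** The Study design section describes a study "with four intervention and eight matched comparison sites in GM: two comparison sites per intervention site". Under Observation schedule and procedure, each site is visited on two days with four periods a day, "resulting in a total of eight observation periods for each site at each time point", and "this schedule will be replicated at all follow-ups".

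The Main analysis section sets the endpoint: "The primary outcome will be a count per observation period of Take Notice behaviour at 12 months". It says effects will be judged "compared to the two corresponding comparison sites". The model is then written out in three steps:

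1. On baseline data, choose a Poisson, zero-inflated Poisson or normal regression on weather, day and time, plus the older-adult count when a behaviour is analysed.
2. Apply that model to the combined pre- and post-intervention data.
3. "Thirdly, we will add into the model Group (intervention or comparison) and Period (pre or post"), with the Group-by-Period coefficient as the treatment effect.

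The method is called a difference-in-differences analysis, "adapted because we do not have a before and after measure at the level of the hour".

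The Power calculation section takes a different view of the data. It uses a matched-pair cluster method: "calculate the number of clusters required for a completely randomised cluster design", then reduce that number by the correlation between the matched groups. It assumes eight periods per cluster and an ICC of 0.02.

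**The concern.** The site is the unit that was or was not greened. The model as written uses 12 x 8 x 2 = 192 rows for baseline and 12 months and treats them as independent given the covariates. A two-level Group term also pools all eight comparison sites, so the promised contrast with each site's own two matches does not appear in the model.

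The reason given for the adaptation does not explain leaving site out. There may be no paired measure for a given hour, but the same 12 sites are measured before and after on the same schedule, so a paired measure exists at site level.

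What is at stake is the p-value and confidence interval of the primary outcome. Two kinds of site variation matter, and they act in opposite directions:

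- **Site-by-period variation (drift):** sites move up or down between waves for reasons unrelated to greening. This adds to the variance of the interaction, and a single-level model does not count it.
- **Stable site differences:** these cancel out of a before-after contrast. A normal model without site leaves them in the residual variance and so overstates the standard error.

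**Working it through.** **Inputs from the protocol article.** 4 intervention and 8 comparison sites, m = 8 periods per site per wave, ICC 0.02, control 0.5 (SD 0.77), intervention 1.6 (SD 1.72), two-sided 5%, stated power 99%. The matching correlation r is not stated.

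**The plan's own figure.** Design effect = 1 + 7 x 0.02 = 1.14. SE = sqrt[1.14(1 - r)(1.72²/32 + 0.77²/64)]. With r = 0 this is sqrt(1.14 x 0.1017) = 0.3405, and power = Φ(1.1/0.3405 - 1.96) = 89.8%. With r = 0.3 power is 97.1%, with r = 0.5 it is 99.6%, and r of about 0.43 gives 99%. The 99% can be neither confirmed nor refuted. On this 4-versus-8 layout it depends on a gain from matching, and the analysis model has no term for matching.

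**Variance of the interaction, normal model.** Set the total variance to 1, with stable site share s and site-by-period share v.

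- True variance = 2(1/4 + 1/8)[v + (1 - s - v)/8]
- Single-level model: about 2(1/4 + 1/8)(1/8) = 0.0938, so SE is about 0.306

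With v = 0.02 and s = 0: 0.75(0.02 + 0.98/8) = 0.1069, so the true SE is 0.327. The ratio is 0.306/0.327 = 0.94, and type I error is 2[1 - Φ(1.96 x 0.937)] = 6.6%.

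Simulation under no effect (15,000 runs per scenario) agrees. The last column is a t-test on site-level changes with 10 degrees of freedom.

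| Stable share s | Drift share v | Model SE / true SE | Type I error, no site term | Type I error, site-level change |
|---|---|---|---|---|
| 0 | 0 | 1.00 | 4.8% | 4.9% |
| 0 | 0.02 | 0.93 | 6.6% | 5.1% |
| 0 | 0.10 | 0.76 | 13.9% | 5.4% |
| 0 | 0.20 | 0.63 | 21.4% | 5.1% |
| 0.20 | 0 | 1.10 | 3.1% | 4.8% |
| 0.40 | 0 | 1.24 | 1.7% | 5.4% |
| 0.20 | 0.02 | 1.01 | 4.7% | 5.1% |

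Only the share of 0.02 comes from the article. The other shares are assumptions.

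**Poisson model.** Simulated with mean 0.5 to 1.0 per period and stable log-scale site SD 0 to 0.5. Type I error by assumed log-scale site-by-period SD:

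- no drift: about 5%
- SD 0.2: 6.5% to 9%
- SD 0.4: 12% to 21%
- SD 0.6: 22% to 35%

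To relate these SDs to the stated ICC, the share is μ(exp(σ²) - 1)/[1 + μ(exp(σ²) - 1)]. At mean 0.5, SD 0.2 gives 0.0204/1.0204 = 0.02, which is the stated value. SD 0.4 gives 0.08 at mean 0.5 and 0.15 at mean 1.0. SD 0.6 gives 0.18 and 0.30. The range of 12% to 35% thus assumes drift of about 4 to 15 times the stated ICC.

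**Normal model on simulated counts.** With stable log-scale site SD 0.8 and no drift, type I error falls to about 2% to 3%.

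All simulations omit the covariates and zero inflation.

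**The case against.** **The article is condensed and the analysis plan is not shown.** Variance estimation may be set out there, and the promise to compare with the corresponding sites suggests that matching was meant to count. This has some weight. However, the article lists the model terms step by step, names three single-level distributions, and presents itself as an a priori specification. Following it as written leaves site out.

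**The older-adult count is a covariate for Take Notice.** Changes in footfall are an obvious source of drift, and this covariate may absorb part of it. This stands, so the larger error rates may be overstated.

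**Over-dispersion will be checked.** This helps little. The check uses baseline data only, and one wave cannot show how sites change between waves. None of the three distributions models correlation within a site.

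**At the stated ICC the error is modest.** This also stands. The 6.6% treats the entire ICC as drift and is therefore an upper figure for that ICC.

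A reader might infer that the primary interval is wrong whatever happens, or always too narrow. The document does not support that: the Poisson model holds about 5% when sites do not drift, and in the normal model the two errors can cancel (4.7% in the last table row). A reader might also take the shared census areas in Table 1 (3A, 4A and 4B; 2B and 3B; intervention sites 3 and 4) as proof of further dependence. They show shared area-level characteristics, not correlated Take Notice counts, and no effect can be derived from them.

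**Conclusion.** The point holds as an inconsistency between a study planned as a matched cluster design and a primary model with neither cluster nor matching. The supported conclusion is that the standard error of the Group-by-Period effect is not protected, not that it must be wrong in a known direction.

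The size depends on a drift variance that the article does not give. On its only clustering figure, type I error is at most about 6.6% in the normal model. The Poisson range of roughly 12% to 35%, and the 2% to 3% for the normal model with large stable differences, rest on assumed variances and on simulations without the older-adult count.

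The point still needs correcting before the 12-month analysis. It concerns the primary test, the true drift is unknown, and a site-level analysis held close to 5% in every scenario examined.

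**What to change.** In step three, use one of two routes:

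- **Model:** add site as a 12-level term, which absorbs the Group and matched-set main effects. Keep Period and Group-by-Period, and allow for site-by-period variation.
- **Site-level change:** compute 12-month minus baseline for each site and contrast each intervention site with its two matched comparison sites.

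Either way, base inference on site-level degrees of freedom, not on an observation-level z: about 10 for 12 sites, or about 3 if analysed as four matched sets. State which in advance.

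A permutation of the intervention label within matched triplets (3^4 = 81 arrangements, smallest p = 1/81 = 0.012) can serve as an optional sensitivity check only. Sites were not randomised, so it has no design basis as a confirmatory test.

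The cost is a wording change and a somewhat different model, with no new data. The confidence interval may widen: the critical value rises from 1.96 to about 2.23 with 10 degrees of freedom (factor 1.14) or about 3.18 with 3 (factor 1.62), before any gain in precision from removing stable site or matched-set differences.

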**Fig. 3 Fig3:**
[figure not shown]
Observation schedule for two observers during baseline data collection for all intervention and comparison sites. The two columns within each day correspond to the two observers i.e. one column for each observer. The numbers/ letters refer to intervention and comparison sites e.g. ‘1’ is Intervention site 1, and ‘1A’ and ‘1B’ are the corresponding comparison sites: Comparison site 1A and Comparison site 1B, respectively. See Table 1 for details on each intervention and comparison site

The same procedure will be used as set out in the MOHAWk observation manual (Additional file 2). All observers will be trained in using MOHAWk and will be required to demonstrate high agreement with the trainer before making observations in the present study. Prior to observations, observers will visit each site to agree on the boundaries of the target area in which all participants will be recorded. Target areas are of similar size between corresponding intervention and comparison sites, and the same target areas will be used at all time points (see Additional file 3).

Data will be recorded using pencil and paper. Data will be entered into SPSS at each time point once data collection is completed.

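### The stated reason for adapting the difference-in-differences conflicts with the replicated observation schedule, and the model leaves 96 planned before-and-after slot pairs unlinked

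*Protocol article*

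**What the plan says.** Under Main analysis, baseline and follow-up observation periods are pooled ("we will combine the pre- and post-intervention data together and apply the model from step one"), and Group, Period and their interaction are then added. The interaction is the treatment effect. The named covariates are weather, day and time, plus the overall older-adult count when a behaviour such as Take Notice is the outcome. No site, matched-set or slot term is named. The approach is called a form of difference-in-differences, "adapted because we do not have a before and after measure at the level of the hour".

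Under Observation schedule and procedure, each site is observed on two weekdays at four fixed clock hours (10–11, 12–1, 3–4 and 5–6), "resulting in a total of eight observation periods for each site at each time point". Of the baseline timetable the protocol says "this schedule will be replicated at all follow-ups". A missed session is "rescheduled for the same day of the next available week". The same section adds that "the same target areas will be used at all time points".

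**The concern.** The two sections cannot both be right as worded. The unit of analysis is a count per observation period, and the schedule measures each site's weekday-and-hour slot at baseline and again at each follow-up. That is a before-and-after measure at the level of the hour.

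The stated premise leads to a model in which baseline and follow-up hours are unlinked rows. Day and time enter only as effects common to all sites. They cannot represent a slot that is persistently busy at one site and quiet at another. Under some of the candidate models this stable variation stays in the residual and enlarges the standard error of the Group-by-Period effect. The protocol itself expects small effects, so precision matters.

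**Working it through.** **The plan's own figure.** The protocol gives no standard error and no within-slot correlation, so there is nothing to reproduce on this point. Its 99% power figure depends on a matching correlation that is not stated. With unequal variances and a design effect of 1 + 7 × 0.02 = 1.14, power is 89.8% at a matching correlation of 0 and about 99% at 0.43. The figure is attainable, and nothing here rests on it.

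**Number of pairs.** There are 4 + 8 = 12 sites and 8 periods per site per wave. That gives 96 slots per wave, 32 intervention and 64 comparison. Baseline against 12 months is therefore 192 rows, or 96 pairs.

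**Linear model, closed form.** Let σ be the SD of a count and ρ the correlation between a slot's baseline and follow-up counts, beyond common day and time effects.

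- Unpaired SE = √[2σ²(1/32 + 1/64)]
- Paired SE = √[2σ²(1−ρ)(1/32 + 1/64)]
- Unpaired/paired = 1/√(1−ρ)

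With σ = 0.77 throughout (the control SD in the power calculation), the unpaired SE is √(2 × 0.5929 × 0.046875) = 0.236. The paired SE is 0.236, 0.211, 0.183, 0.167 and 0.149 at ρ = 0, 0.2, 0.4, 0.5 and 0.6. All values of ρ are assumptions. These SEs ignore site-level clustering.

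**Simulation.** Assumptions: Poisson counts with mean 1, gamma slot effects of variance v, 4 against 8 sites, 8 slots, and no site-by-period variation. Then ρ = v/(1+v).

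| v | ρ | Linear SE, no slot term | Linear SE, paired | Actual spread (linear) | Poisson SE, no slot term | Actual spread (Poisson, log scale) |
|---|---|---|---|---|---|---|
| 0 | 0 | 0.306 | 0.305 | 0.306 | 0.310 | 0.305 |
| 0.25 | 0.20 | 0.341 | 0.305 | 0.311 | 0.311 | 0.312 |
| 0.5 | 0.33 | 0.373 | 0.305 | 0.308 | 0.311 | 0.315 |
| 0.75 | 0.43 | 0.401 | 0.304 | 0.314 | 0.313 | 0.318 |

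Under the linear model, pairing lowers the SE by about 11%, 18% and 24% in the last three rows, and the paired SE is the one that matches the actual spread. Under plain Poisson the unpaired SE is already about right. If the Poisson SE is scaled for over-dispersion, the excess returns: at v = 0.25 it is 0.346 against 0.312. The zero-inflated Poisson option was not computed.

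**Point estimate.** In one simulated balanced data set, a linear fit with day and time only and a fit with slot effects gave the same Group-by-Period estimate, 0.234. This concerns the standard error, not bias.

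**Sites that change differently over time.** In the linear model at v = 0.25, with an assumed site-by-period variance added:

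| Site-by-period variance | SE, site terms only | SE, slot-paired | Actual spread |
|---|---|---|---|
| 0.05 | 0.345 | 0.314 | 0.365 |
| 0.1 | 0.349 | 0.321 | 0.420 |

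Both are too small here, and the slot-paired SE is further from the truth.

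**The case against.** The strongest defence is that the clause describes repeated cross-sections: different people pass on different dates, so no individual hour is measured twice. That describes the data fairly, but it does not rescue the wording. The analysis counts per observation period, and the schedule repeats the period. The schedule figure is not shown, so slot identity rests on the text; the text is explicit about clock hours, weekday retention and replication.

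Several other objections stand and limit the point.

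- A reader might infer that the baseline counts are collected and then ignored. They are not: they build the step-one model and form the pre-intervention rows. Only the pairing is unused.
- A reader might infer that the primary standard error is necessarily too large. That fails under plain Poisson, one of three named candidates. It also fails under the linear model if sites drift apart over time, when the error runs the other way.
- For Take Notice, the overall older-adult count is an hour-specific measure of how busy the slot is. It may remove part of the slot variation, so the linear figures may overstate the loss for the primary outcome. The secondary outcome, the overall count itself, has no such covariate.
- Slot fixed effects are not cheap: 96 − 12 = 84 parameters beyond site terms, before allowing for the day and time terms they absorb, on 192 rows.

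**Conclusion.** The contradiction stands: the reason given for adapting the analysis is at odds with the study's own schedule, and 96 planned pairs per contrast go unused as pairs. The consequence is conditional. If the normal model or an over-dispersion-scaled model is chosen, stable slot (and site) variation stays in the residual. In the linear case the standard error is then too large by about 1/√(1−ρ): 1.12 at ρ = 0.2, 1.22 at 0.33, 1.41 at 0.5, and no excess at 0. This assumes a balanced design, no site-by-period variation and a ρ that the document does not supply. Under plain Poisson there is essentially no loss.

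The documents do not support a claim of bias, or of a fixed loss of power. Nor would a slot term by itself put the inference right, because it does nothing about site-level change.

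**What to change.** 1. Delete or correct the clause. State that each follow-up period corresponds to the baseline period of the same site, weekday and clock hour, or explain why that pairing is not used.
2. Label every session with its site-weekday-hour slot, giving a rescheduled session the label of the slot it replaces.
3. Add a slot random intercept nested in site to the Group-by-Period model, or analyse slot-level change. Either avoids the 84 extra parameters of slot fixed effects.
4. Base the standard error on the site as the cluster, for example through a site-by-period random effect or cluster-robust inference with a small-sample correction, since there are only 12 sites.

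No new data are needed. The cost is a corrected sentence and slightly more modelling work. The site-based standard error may turn out larger than the naive one, and that should be accepted in advance.
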